| 
Methodology:
 
This is a Phase 1/2 study to evaluate the safety and potential efficacy of agenT-797, an unmodified, allogeneic iNKT cell therapy, in patients with moderate to severe ARDS secondary to SARS-CoV-2 or influenza, either with intubation or at high risk to be intubated, as determined using Berlin definition(s) (ARDS 2012).
 
Completed: Part 1 will employ a standard 3+3 dose escalation design of agenT-797. All patients will receive a single infusion of agenT-797. Patients will also receive other treatments and supportive care per discretion of the Principal Investigator. Once the maximum tolerated dose of agenT-797 has been cleared in Part 1, an Expansion Cohort will be opened. A Safety Monitoring Committee (SMC) will be established to assess safety and decide on escalation to next cohort and expansion dose, as well as any protocol modification to include less severe cases.
 
Part 2 (Expansion) of the study will evaluate an additional cohort in up to 15 patients:
 
 
Cohort 4 – patients with moderate to severe ARDS secondary to SARS-CoV-2 or influenza, according to Berlin definition, who are on mechanical intubation
 
 
The SMC will continue to review safety.
 
Screening:
 
Prior to any Screening activities, the patient (or legal representative) must sign an informed consent form and will proceed to undergo full screening procedures to determine eligibility. Full human leukocyte antigen-typing (blood) will also be performed.
 
Eligible patients will be treated with agenT-797 on Day 1. Assessments will be obtained through Day 32 or until discharge from hospital. Safety follow-up will occur 30 days after discharge, the patient to then be contacted regarding serious adverse events (SAEs) and to confirm survival up to 6 months after hospitalization.
 |                                                                                                                                                                                   |

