#### **4.10. 30-DAY AND SAFETY FOLLOW-UP**

The Safety Follow-up period will be 30 days, and the patient will be contacted by telephone 3 and 6 months after discharge regarding any SAEs and to confirm survival, as feasible. The first Safety Follow-up Visit will be at Day 30 ( $\pm 2$ ), or at EOH. If a patient is discharged at Day 30, 30-day Follow-up will be the same as EOH. Please refer to [Table 3](#).

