### **8.1.10. Reporting of Serious Adverse Events**

All SAEs must be reported from the time of ICF signature through 6 months in the Safety Follow-up period after infusion with agenT-797, and followed-up until resolution, if feasible.

All SAEs must be reported to the Sponsor within 24 hours of the first awareness of the event.

Any death, SAE, or pregnancy (including pregnancy of a partner) experienced by a patient regardless of relationship to study drug, or any death that occurs within 6 months after receiving study drug, must be promptly reported (within 24 hours of the Investigator becoming aware of the event) in the CRF and/or via email.

AESIs, even if they do not meet the serious criteria, must be reported using the SAE form and in an expedited manner (within 24 hours of the Investigator becoming aware of the event), but should be noted as non-serious on the SAE form and the AE CRF ([Section 8.1.3](#)).

The Investigator must complete, sign and date the SAE pages, verify the accuracy of the information recorded on the SAE pages with the corresponding source documents.

For overdoses associated with a SAE, standard reporting timelines apply ([Section 8.1.6](#)).

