| 
 
To assess evidence of improvement and resolution of ARDS following infusion with agenT-797
 
To assess avoidance of multiorgan dysfunction syndrome
 
 | 
 
Assessment of ventilator-free days
 
Time to extubation
 
Time to intubation in patients with mild ARDS
 
Vital signs and physical examination findings
 
Lung injury score (LIS): The LIS is a composite 4-point scoring system including the PaO2/FiO2, positive end-expiratory pressure (PEEP), quasi-static respiratory compliance, and the extent of infiltrates determined by imaging
 
Intensive care unit-free days
 
Mean daily sequential organ failure assessment score(s) (SOFA)
 
Supportive interventions used (e.g., use of prone ventilation, paralytics, pulmonary vasodilators, and other interventions affecting oxygenation)
 
All-cause mortality rates within 30 days and at 6 months
 
 | 
 
Proportion of ventilator-free days and the corresponding 95% CI
 
Median time to extubation from dosing and the corresponding 95% CI
 
Median time to intubation from dosing in patients with mild ARDs and the corresponding 95% CI
 
Median time of intubation and the corresponding 95% CI
 
Proportion of intensive care unit-free days and the corresponding 95% CI
 
Listings of vital signs and physical examination
 
Proportion of all-cause mortality within 30 days and at 6 months and their corresponding 95% CIs
 
Plots and listings of LIS over time
 
Plots and listings of median daily SOFA score over time
 
 |

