### 4.2 General Presentation Considerations

Baseline is defined as the last available pre-treatment assessment. The end of the study is defined as the date on which the last subject completes the final follow-up visit, which may be up to 6 months after the last subject's screening date. Treatment day will be calculated relative to the date of the first treatment day such that Treatment Day = Assessment Date – First Infusion Date + 1. 6

Continuous data will be summarized in terms of the mean, standard deviation (SD), median, upper quartile, lower quartile, minimum, maximum and number of observations, unless otherwise stated. The minimum and maximum will be reported to the same number of decimal places as the raw data recorded in the database. The mean, median, lower quartile and upper quartile will be reported to one more decimal place than the raw data recorded in the database. The SD will be reported to two more decimal places than the raw data recorded in the database. In general, the maximum number of decimal places reported shall be four for any summary statistic.

Categorical data will be summarized in terms of the number of patients providing data at the relevant time point (n), frequency counts and percentages.

Percentages will be presented to one decimal place. Percentages will not be presented for zero counts.

Changes from baseline in categorical data will be summarized using shift tables where appropriate.

P-values greater than or equal to 0.001, in general, will be presented to three decimal places. P-values less than 0.001 will be presented as “<0.001”.

Wilson confidence intervals (CIs) will be presented to one more decimal place than the raw data.

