#### **4.11.1.1 Handling of Dropouts or Missing Data**

No imputation will be made for missing data resulting from an early withdrawal, missed evaluations, or any other unforeseen reason. All missing or partial data will be presented in the patient data listings as they are recorded on the eCRF.

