#### **4.11.2.4 All-case mortality**

Proportion of death from all causes within 30 days and at 6 months and its 95% score CI will be calculated. It is a direct measurement of efficacy of the therapy.

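### Six-month mortality has no stated time origin and no rule for patients who cannot be reached, and the SAP's end-of-study clause does not fit a call six months after discharge

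*Combined protocol and SAP*

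**What the plan says.** All-cause mortality within 30 days and at 6 months is a secondary endpoint (protocol section 3). SAP 4.11.2.4 plans: "Proportion of death from all causes within 30 days and at 6 months and its 95% score CI will be calculated". SAP Table 2 gives the estimator as "Proportion of all-cause mortality within 30 days and at 6 months and their corresponding 95% CIs". Neither place states the date from which six months is counted.

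The time references elsewhere are:

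- Protocol 4.10, repeated in SAP 3.9: "the patient will be contacted by telephone 3 and 6 months after discharge regarding any SAEs and to confirm survival, as feasible".
- Protocol synopsis, Methodology: contact is "to confirm survival up to 6 months after hospitalization".
- Protocol 8.1.10: serious adverse events are reportable "through 6 months in the Safety Follow-up period after infusion with agenT-797". The same section requires prompt reporting of any death within six months of receiving study drug.
- SAP 4.2: the study ends when the last subject completes the final follow-up visit. The SAP adds that this may be "up to 6 months after the last subject's screening date".
- Synopsis: "Safety follow-up will occur 30 days after discharge". Protocol 4.10 and Table 3 place that visit at Day 30 (±2), and 4.10 also allows end of hospitalization.

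On missing data, SAP 4.11.1.1 says "No imputation will be made for missing data resulting from an early withdrawal", and extends this to missed evaluations and other reasons. SAP 4.2 summarizes categorical data among patients who have data at the time point. SAP 4.11.2 bases clinical activity on the safety analysis set, which is everyone who received agenT-797.

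**The concern.** A proportion dead at six months is interpretable only if every patient is followed over the same interval and it is known who is in the denominator. Here the survival calls are tied to discharge and the death-reporting window to infusion, so two analysts following the documents could classify the same death differently. A discharge clock also cannot serve as a common time zero, because a patient who dies in hospital has no discharge date.

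The second gap is the patient discharged alive and never reached. SAP 4.2 and 4.11.1.1 together point to leaving that patient out. SAP 4.11.2 would equally allow keeping the patient in the denominator. No censoring method is given. SAP 4.11.2.4 presents mortality as a direct measure of the therapy's efficacy, so the unstated choice bears on a result that readers will look for.

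**Working it through.** The documents give no expected six-month mortality, loss rate or length of stay, so there is no planned figure to reproduce. The rates and stays below are assumptions, except that the longest stay (84 days) is the synopsis's 12-week intervention period.

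**1. Effect of the clock on time at risk.** Take six months as 180 days. On the discharge clock, time at risk from infusion is stay + 180.

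- Stay 7 days: 7 + 180 = 187 days
- Stay 32 days: 32 + 180 = 212 days
- Stay 84 days: 84 + 180 = 264 days

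On the infusion clock it is 180 days for everyone. As an example, a patient discharged 60 days after infusion who dies 200 days after infusion is dead at six months on the discharge clock (200 < 240) and alive on the infusion clock (200 > 180).

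**2. End-of-study clause.** Screening may precede infusion by 0 to 4 days (protocol 4.5.5). For the last subject, the shortfall is (discharge + 6 months) − (screening + 6 months) = screening interval + stay.

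- Stay 7 days: 7 to 11 days
- Stay 32 days: 32 to 36 days
- Stay 84 days: 84 to 88 days

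On the infusion clock the shortfall is only 0 to 4 days. Suppose the clause were enforced as a calendar cut-off, with the 7-day stagger between patients and equal stays. Calls would then be lost for the last 1–2, 5–6 or 12–13 patients respectively, and for no earlier patient.

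**3. Leaving out unreached patients when only survivors are lost.** With true mortality m and a fraction l of survivors unreached, the observed proportion is m / [m + (1 − m)(1 − l)].

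| m | l = 10% | l = 20% | l = 30% |
|---|---|---|---|
| 40% | 0.40/0.94 = 42.6% | 0.40/0.88 = 45.5% | 0.40/0.82 = 48.8% |
| 30% | 0.30/0.93 = 32.3% | 0.30/0.86 = 34.9% | 0.30/0.79 = 38.0% |

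**4. The direction is not fixed.** Deaths after discharge can also be missed. Assume true mortality of 40% (30 points in hospital, 10 after discharge), with 60% of post-discharge deaths and 10% of survivors missed. Observed deaths are 0.30 + 0.04 = 0.34 and observed survivors 0.60 × 0.90 = 0.54. The estimate is 0.34/0.88 = 38.6%, below the truth.

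**5. Spread from the denominator alone.** Assume N = 43 (the planned maximum, for illustration), 13 known deaths and 9 discharged patients unreached. Wilson 95% intervals are in brackets.

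- Patients with data only: 13/34 = 38.2% (23.9 to 55.0)
- All treated, unreached counted alive: 13/43 = 30.2% (18.6 to 45.1)
- All treated, unreached counted dead: 22/43 = 51.2% (36.8 to 65.4)

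With 4 unreached the three figures are 33.3%, 30.2% and 39.5%. With none unreached, all are 30.2%.

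**6. Kaplan-Meier on similar data.** Assume 43 patients, 13 early deaths, then 9 censored, then 2 later deaths among the 21 still followed. Mortality is 1 − (30/43)(19/21) = 36.9%. The proportion among patients with data is 15/34 = 44.1%, and counting the unreached as alive gives 15/43 = 34.9%.

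**The case against.** The strongest reply is that this is a descriptive, single-arm study with no hypothesis tests, that deaths are listed by subject, and that the gaps are ones of wording. Several stronger readings are also tempting and should be resisted.

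- A reader might count four competing clocks. The synopsis ties its post-hospitalization contact to discharge, so that is the same origin as protocol 4.10. The screening date qualifies the end of study, not the endpoint. Two origins remain: discharge and infusion.
- A reader might infer that the SAP closes the study before the last calls can be made. The operative definition is the last subject's final follow-up visit, and SAP 3.9 repeats the calls six months after discharge. Only the added clause conflicts.
- A reader might take a complete-case proportion as specified. It is the natural reading of SAP 4.2 with 4.11.1.1, but SAP 4.11.2 also permits all treated patients.
- A reader might conclude that mortality will be overstated. Step 4 shows that the sign can reverse. The 24-hour reporting rule runs from the investigator's awareness, so a death in an unreached patient can be missed too.

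The 30-day estimate is little affected. SAP 4.2 counts treatment days from infusion, protocol 4.5.3 refers to deaths within 30 days of administration, and only the synopsis differs on the visit. An in-hospital death within six months of infusion also counts as dead on either clock.

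Kaplan-Meier is not a complete answer either. Censoring may be informative, and a log-log interval fails in a cohort with no deaths, a real prospect where Cohorts 1 and 2 have three to six patients. These points limit the claim and shape the fix. They do not supply the missing six-month origin or the rule for unreached patients.

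**Conclusion.** The point holds in a limited form. The six-month mortality estimate has no stated origin, the documents support two that conflict, and unreached patients have no defined place in the analysis. On the discharge clock, time at risk exceeds that on the infusion clock by the length of stay, 7 to 84 days in the illustration.

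The bias from loss to follow-up is a risk of unknown size and direction, and is zero if all patients are reached. Under the one-sided assumption that only survivors are lost, 40% would read as 43% to 49% with 10% to 30% of them unreached. With 9 of 43 unreached, the denominator rule alone moves the reported figure between 30.2% and 51.2%.

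The SAP 4.2 clause is a separate and smaller inconsistency that could touch only the last-enrolled patients. The documents do not establish that follow-up will be truncated or that the estimate will be biased upward.

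**What to change.** - **SAP 4.11.2.4 and Table 2.** Set time zero at infusion for all treated patients. Estimate mortality at Day 30 and Day 180 by Kaplan-Meier, censoring at the date last known alive.
- **Sensitivity.** Because censoring may be informative, report best-case (unreached alive) and worst-case (unreached dead) proportions on the all-treated denominator with the planned score interval. Keep the score interval for small cohorts and for cohorts with no deaths.
- **SAP 4.2.** Define the end of study as the last patient's final six-month post-discharge contact and remove the screening-based limit.
- **Protocol.** Reconcile the synopsis timing of the 30-day follow-up with section 4.10 and Table 3.

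No new contacts are needed. A call six months after discharge always falls after six months from infusion, and the three-month call supplies a later censoring date for patients lost afterwards. The cost is SAP wording, a one-line protocol clarification, a little more analysis work, and results that are less simple to read than a single percentage.

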#### **4.11.2.5 Decrease in viral burden from upper respiratory track samples collected sequentially under treatment**

A longitudinal analysis and plot of the viral burden from upper respiratory track samples collected of each patient will be provided.

#### **4.11.2.6 Persistence of allogeneic iNKT cells**

A longitudinal analysis and plot of the amount of allogeneic iNKT cells will be provided.

#### **4.11.2.7 Baseline and every 24 hours: complete blood count with differential, comprehensive metabolic panel, procalcitonin, B-type natriuretic peptide, fibrinogen, prothrombin time, partial thromboplastin time, magnesium, angiotensin II level**

Longitudinal analyses and plots of all these biomarkers will be provided.

#### **4.11.2.8 Available image (X-ray, CT-scans) to evaluate ARDS**

Longitudinal analyses and plots for every measurement based on available image to evaluate ARDS will be provided.

#### **4.11.2.9 Change in lung fitness through assessment of respiratory function**

A longitudinal analysis and plots of a respiratory functional score (LIS score) will be provided.

#### **4.11.2.10 Time from dosing to viral clearance**

Median time from dosing to viral clearance will be estimated.

#### **4.11.2.11 Prevention of secondary infections**

Proportion of patients with developed secondary infections will be computed together with its 95% score CI.

#### **4.11.2.12 SOFA score**

The SOFA score(s) will be determined for each patient at specific timepoint as specified in Table 4, Schedule of Assessment, and will be used to assess the presence, number, and severity of organ dysfunction in six organ systems.

#### **4.11.2.13 Measurement of allo antibodies against HLA class 1 and class 2 molecules**

The presence of panel reactive antibodies (PRA) will be determined for HLA class I and HLA class II by flow cytometry. The ID of the PRA detected in patient serum samples will be correlated with the known donor tissue type by virtual crossmatch, to determine the presence of Donor Specific Antibodies (DSA) in patient serum. The presence of PRA and DSA in patient serum will be determined pre infusion of agent-797, and at specific timepoints post infusion, as defined in Table 4, the Schedule of Assessment.

#### **4.11.2.14 RNA analysis of epithelial cells**

The health of epithelial cells will be evaluated by an RNA analysis at specific timepoints as defined in Table 4, the Schedule of Assessment.

### **4.11.3 Safety Evaluation**

The DLT analysis set will be used for the DLT rate and MTD of agentT-797. The safety analysis set will be used for all other safety analyses.

### **4.11.4 Adverse Events**

An AE is any untoward medical occurrence in a study subject administered an investigational medicinal product (IMP) which does not necessarily have a causal relationship with this treatment. An AE can therefore be any unfavorable and unintended sign (including a clinically significant abnormal laboratory finding), symptom, or disease temporally associated with the use of an IMP, whether or not considered related to the IMP. Adverse events may include the onset of new illness and the exacerbation of pre-existing conditions.

Other untoward events occurring in the framework of a clinical study will be recorded as AEs, e.g. those occurring during treatment-free periods (including screening or post-treatment follow-up periods), in association with study-related procedures and assessments.

Concomitant illnesses, which existed before entry into the clinical study, will not be considered AEs unless they worsen during the treatment period. Pre-existing conditions will be recorded as part of the subject's medical history.

A treatment-emergent adverse event (TEAE) is defined as an AE that begins or that worsens in severity after at least one dose of the study drug has been administered.

Any AEs with incomplete start and end dates/times will be treated as follows:

Adverse events with unknown start and/or end times (but where the date is known) will be imputed with a time of 00:00 h for the tabulations but will be shown as NK: NK in the listings (where NK = Not Known).

Adverse events with completely unknown start dates will be considered as treatment-emergent for the tabulations and will be shown as NK in the listings. Partially complete AE dates will not be imputed in the listings and the available day, month and year components will be used to determine if an adverse event is treatment-emergent taking the first dosing date and end of study date as references.

Adverse events will be coded using the MedDRA version 22.0 or higher.

The relationship or association of the study medication in causing or contributing to the AE will be characterized by the Investigator using the following classification and criteria:

- Possibly or probably related: A clinical event, including laboratory test abnormality, with a reasonable time sequence to study medication administration that might or might not be also explained by concurrent disease or other drugs or chemicals.
- Not related: A clinical event, including laboratory test abnormality, judged to be clearly and incontrovertibly due to extraneous causes (e.g., diseases, environment), or with a temporal relationship to study medication administration that makes a causal relationship improbable, and/or for which other drugs, chemicals, or underlying diseases provide a much more plausible explanation.

Severity or intensity will be assessed according to the NCI CTCAE version 5.0 severity grading scale. Grade refers to the severity of the AE. The NCI CTCAE version 5.0 displays Grades 1 through 5 with unique clinical descriptions of severity for each AE based on this general guideline:

- Grade 1: Mild (awareness of sign or symptom, but easily tolerated)
- Grade 2: Moderate (discomfort sufficient to cause interference with normal activities)
- Grade 3: Severe (incapacitating, with inability to perform normal activities)
- Grade 4: Life-threatening (urgent intervention indicated)
- Grade 5: Death related to AE.

The following summaries will be generated based on safety analysis set by dose level and overall:

- A summary of the number and percentage of patients reporting an AE by SOC and PT.
- A summary of the number and percentage of patients reporting a TEAE by SOC and PT.
- A summary of the number and percentage of patients reporting a related TEAE by SOC and PT.
- A summary of the number and percentage of patients reporting a TEAE by severity, SOC and PT.
- A summary of the number and percentage of patients reporting a TEAE by causality, SOC and PT.

AE summaries will be ordered in terms of decreasing frequency for SOC, and PT within SOC, in the overall group, and then alphabetically for SOC, and PT within SOC.

For each subject and each adverse event, the worst severity recorded will be attributed and used in the by-severity summaries. Similarly, the worst causality (most related to treatment) will be attributed and used in the by-causality summaries. If severity or causality is missing, a conservative approach for AE assessment (taking into account the worst case) will be followed.

A by-subject listing of all AEs (including non-treatment-emergent events) will be provided. This listing will be presented by dose level and will include center, subject identifier, age, sex, race, adverse event (SOC, PT, and verbatim term), date of onset, date of resolution, duration, severity, seriousness, action taken, outcome and causality.

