### 8.1.4. Dose-Limiting Toxicity Criteria

The DLT observation period is defined as 14 days after infusion of agenT-797. The nature, frequency, time to onset, severity of toxicities, medical history, and concomitant medication, as well as the success of standard medical management, will be analyzed to determine if a given toxicity should be considered a DLT by the SMC per charter.

A DLT is defined as any of the following at least possibly related AEs graded using NCI-CTCAE v5.0:

- General:
  - Any Grade 4 or 5 toxicity
- Hematologic:
  - Any Grade 3 hematologic toxicity that lasts for more than 7 days despite treatment

- Non-hematologic:
  - Any Grade 3 non-hematologic toxicity that lasts for more than 72 hours despite adequate treatment
  - Exceptions: Grade 3 events with a different definition of duration that are considered DLTs are the following:
    - Grade 3 renal or hepatic toxicity that lasts 7 days or longer
    - Any Grade 3 or higher toxicity that is cardiac, respiratory, or neurologic of any duration
- Immune:
  - Any Grade 2 acute GVHD that requires steroid therapy for > 7 days or that has progression of clinical signs and symptoms after 3 days of steroids or that has partial response after 14 days of treatment, or GVHD Grade 3 or higher
  - Any **new** Grade 3 CRS lasting more than 72 hours and/or **new** Grade 4 CRS of any duration at least possibly related to agenT-797. For patients presenting with Grade 2 or 3 CRS at baseline, worsening of baseline CRS grade, judged as at least possibly related to agenT-797, and occurring within 4 hours of infusion ([Lee 2019](#))
  - Any clinically significant Grade 3 autoimmune disorder that lasts for more than 72 hours at Grade 3 despite adequate treatment or any Grade 4 autoimmune disorder of any duration

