## **4.10 Treatment Exposure / Compliance**

### **4.10.1 Treatment Exposure**

AgenT-797 will be administered as a single intravenous infusion of allogeneic iNKT cells over 10 to 30 minutes on Day 1. The extent of the exposure to agenT-797 will be summarized and presented based on the safety analysis set, by dose level and overall. The summary will include:

- Duration of agenT-797 administration, defined as the number of minutes between the administration start time and the end time
- Calculated dose level
- Actual dose level

A by-subject listing of exposure data will be provided.

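### Setting unknown AE start times to 00:00 can class infusion-day events as pre-dose, and the SAP does not say whether treatment-emergent status is judged by date or by date and time

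*Combined protocol and SAP*

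**What the plan says.** SAP 4.11.4 (Adverse Events) defines a TEAE as "an AE that begins or that worsens in severity after at least one dose of the study drug has been administered". It then gives three rules for incomplete dates and times:

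- **Date known, time unknown.** The event "will be imputed with a time of 00:00 h for the tabulations". The listings show the time as not known. The rule covers start and end times and makes no exception for the infusion day.
- **Start date completely unknown.** "Adverse events with completely unknown start dates will be considered as treatment-emergent for the tabulations".
- **Date partly known.** The available day, month and year "will be used to determine if an adverse event is treatment-emergent taking the first dosing date and end of study date as references".

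On dosing, SAP 4.10.1 (Treatment Exposure) states: "AgenT-797 will be administered as a single intravenous infusion of allogeneic iNKT cells over 10 to 30 minutes on Day 1". The same section derives the duration of administration from its start and end times, so the clock time of the infusion is on file.

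**The concern.** Treatment is a single infusion, so Day 1 is the only day on which clock time decides whether an event came before or after the dose. It is also when infusion-related and hypersensitivity reactions are most likely. Protocol 8.1.3 makes those of Grade 2 or higher events of special interest if they occur during the infusion or in the following 24 hours. Midnight at the start of Day 1 cannot fall after the infusion. If TEAE status is programmed on date and time, the default therefore moves a post-infusion event with no recorded start time to the wrong side of the dose.

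The primary endpoint is the number and severity of AEs and DLTs. The table of all AEs in SAP 4.11.4 is by system organ class and preferred term only. Severity, relatedness and causality are tabulated for TEAEs alone, and the serious-event table and listing in SAP 4.11.5 are also restricted to TEAEs. The only AESI summary there covers those leading to discontinuation of study treatment. A graded infusion reaction that did not stop the infusion therefore depends on the TEAE tables to appear with its grade in any table.

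**Working it through.** The plan gives no figure to reproduce here. All analyses are descriptive, and nothing below depends on alpha, power or sample size. The check is one of logic, followed by simple arithmetic on the denominators.

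**Step 1: the classification.** Let *d* be the infusion start on Day 1, in minutes after midnight (0 to 1439), and *t* the true onset on the same day, with *t* > *d*. The onset time is not recorded, so it is set to 0.

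- Date-time comparison: the event is a TEAE if imputed onset > *d*, that is, if 0 > *d*. This is false for every *d*.
- Date comparison: the event is a TEAE if onset date ≥ dosing date, that is, if Day 1 ≥ Day 1. This is always true.

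The number of possible (*d*, *t*) pairs is 1440 × 1439 / 2 = 1,036,080. Enumerating them all gives:

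| Comparison | Post-infusion Day 1 onsets classed as pre-dose | True pre-dose Day 1 onsets classed as TEAE |
|---|---|---|
| Date and time | 100% | 0% |
| Date only | 0% | 100% |

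These percentages apply only to events with an unknown start time. As an invented example, take an infusion at 14:00 and a reaction at 14:20 with no time recorded. Its imputed onset is 14 hours before the dose.

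**Step 2: does another rule override it?** The comparison with the first dosing date is written for partly known dates, and here the date is complete. The default to treatment-emergent is written for wholly unknown start dates, and here the date is known. Neither applies. The definition itself rescues only an event that worsens in severity after the dose.

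**Step 3: is the default consistent with its neighbours?** An AE with no start date is treatment-emergent. An AE known to have started on the day of the infusion is not, on the date-time reading. SAP 4.9 also takes the opposite default for medications: one with a missing or partial date is assumed to be concomitant only, unless there is clear evidence that it started before the first dose.

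**Step 4: where the event appears.**

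- Affected: the tables of TEAEs, related TEAEs, TEAEs by severity and TEAEs by causality (SAP 4.11.4); the serious-TEAE table and listing (SAP 4.11.5); the summary of TEAEs in the DLT period (SAP 4.11.6).
- Not affected: the all-AE table and the by-subject listing of all AEs (SAP 4.11.4); the count of patients with a DLT (SAP 4.11.6).

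**Step 5: size per patient.** If one patient of *n* loses their only qualifying event in a table row, the incidence changes by 100 / *n* points:

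- *n* = 3: 100 / 3 = 33.3
- *n* = 6: 100 / 6 = 16.7
- *n* = 15: 100 / 15 = 6.7

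These sizes come from SAP Table 1 (3 to 6 patients in Cohorts 1 and 2, 6 or more in Cohort 3, up to 15 in Cohort 4). The AE tables are by dose level, and Cohorts 3 and 4 share one dose. If they are pooled at, for example, 6 + 15 = 21, the change is 100 / 21 = 4.8 points.

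**The case against.** The strongest objection is that the SAP never says TEAE status is decided by clock time, and the conventions around it work on dates. Treatment Day is a difference of dates (SAP 4.2), a medication that starts on the dosing date is concomitant (SAP 4.9), and partly known AE dates are compared with the dosing date. On that reading nothing is lost. This stands, and it makes the consequence conditional. It does not remove the problem. AE duration is only listed, so TEAE status is the evident use of an imputed start time in the tables, and the text leaves the choice to the programmer.

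It is also fair that the patients are inpatients with timed checks up to 4 hours after the infusion, so few times may be missing. Footnote g of the schedule limits what is collected before the infusion, which would help to identify most other Day 1 AEs as post-dose. Protocol 8.1.6, however, asks for all AEs from consent, so that help is uncertain.

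Three stronger readings may tempt a reader, and the documents do not support them:

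- **All such events are lost from the safety report.** They remain in the all-AE table and in the full listing, and those that worsen after the dose are still TEAEs. An event with only its end time missing keeps its recorded onset.
- **The 00:00 rule breaks a general worst-case policy.** The sentence saying that "a conservative approach for AE assessment (taking into account the worst case) will be followed" is limited to missing severity or causality. The real inconsistency within the section is with the rule for wholly unknown start dates.
- **Setting end times to 00:00 hides DLTs.** Protocol 8.1.4 does include "Any Grade 3 non-hematologic toxicity that lasts for more than 72 hours despite adequate treatment", and an end time at midnight can shorten a computed duration by just under 24 hours. But the SMC determines DLTs under its charter, the imputation is for tabulations only, and no table of duration is planned. A start time at 00:00 lengthens the duration instead, so the direction is not fixed.

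**Conclusion.** The point holds as a gap in the specification with a conditional consequence. If TEAE status is derived from date and time, every infusion-day AE with an unknown start time that does not later worsen is classed as pre-dose and leaves the TEAE-based outputs. If status is derived from dates alone, none is. The SAP does not exclude the first reading, and the recorded infusion times make it workable.

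The documents do not say how often start times are missing, so the total effect cannot be estimated. The per-patient changes of 33.3, 16.7 and 6.7 points assume that the patient has no other qualifying event in the same row. No test or formal decision rule depends on the result. It matters because the tables at risk are the graded and attributed displays of the primary safety endpoint, in small groups. It should be settled before the TEAE tables are programmed.

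**What to change.** Add one sentence to SAP 4.11.4: an AE whose start date is the infusion date and whose start time is unknown is treatment-emergent, unless the record clearly shows onset before the infusion (for example, an end date and time before it). This follows the logic that SAP 4.9 already uses for medications. A second sentence should say whether TEAE status is otherwise derived from date alone or from date and time.

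The rule keeps all post-infusion Day 1 onsets in the TEAE tables. The evidence condition is needed because a rule based on the date alone would count every true pre-dose Day 1 event as a TEAE. The cost is a short SAP revision and the chance that a few true pre-dose Day 1 events are counted as TEAEs. No change to end-time handling or to duration under the DLT criteria is proposed, because DLT determination belongs to the SMC.
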